**Figure 3 F3:**
[figure not shown]
SPIRIT timetable. ME, maternal education; MS, maternal education; SF 36, Short Form 36; SPIRIT, Standard Protocol Items: Recommendations for Interventional Trials. **This period is approximate. It depends on the availability of EMAeHealth on the Osakidetza-Basque Health Service corporate website.

### Statistical methods

EMAeHealth clinical effectiveness results: quantitative comparisons will be made between intervention and control centres, with an intention-to-treat approach. Mixed models (linear or generalised as appropriate to the variable under study), which take into account the hierarchical structure of the data (patients grouped by midwives, midwives grouped by centre), will be used and 95% CIs will be calculated. Likewise, per-protocol analysis will be carried out, in which the effectiveness of the express use of both the tool in general and in particular of some of its components will be evaluated, adjusting for possible confounding factors. Statistical analysis will be carried out by a professional who is not part of the research team.

Implementation process: For the qualitative evaluation of the tool and its implementation, the analysis of the focus groups, facilitated by the ATLAS.ti software programme, will be structured in three phases: a deductive analysis to determine which CFIR constructs influence its use in real life, followed by an inductive analysis to identify others not included in the CFIR framework that could influence its use, and a third validation phase using triangulation. The analysis results report will be provided to each patient and professional, who will have the opportunity to provide feedback to the team of analysts with their comments (‘response validity’).

For the quantitative evaluation, the distribution of the indicators associated with the use and scope of the tool as well as its components will be described. Measures of central tendency, dispersion and proportions will be calculated, with 95% CIs, and the relationship between the indicators and the predictor/confounding variables will be analysed using mixed models.

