### Random assignment of centres

The eligible centres will be randomised centrally, blindly, and electronically, in the Biocruces-Bizkaia Research Institute, stratified by IHO and in a 1:1 ratio. Therefore, the intervention allocated centres will have access to EMAeHealth, while it will not be accessible for the control group centres. IHOs are groups of health centres within the same geographical area, with similar characteristics and population, under the direction of the same hospital. Therefore, we assume that there are no pre-existing differences in the quality of care provided between centres that belong to the same IHO.

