Indicators of the implementation process: Qualitative indicators: Usability and acceptability of the tool by patients and professionals, as well as barriers and facilitators for its use and adoption in the health system. The qualitative evaluation will be carried out through focus groups of women and professionals, between 6 and 8 per group and as many as necessary until the discourse is saturated.^35^ A semistructured script will be developed for the sessions, based on the theoretical constructs of the CFIR,^28^ which will also serve as the basis for the analysis. The CFIR includes 37 constructs within 5 main domains: intervention characteristics, outer setting, inner setting, individual characteristics and implementation process. Overall, the CFIR aims to help identify potential factors (ie, barriers and facilitators) that are believed to influence implementation. Sessions will be audiorecorded and moderated by an expert in qualitative techniques while an assistant will take notes. Later the sessions will be transcribed and analysed. Quantitative indicators: adoption and frequency of the use of EMAeHealth and its areas according to stratification profiles and correlates with other variables (indicators: patients exposed to the digital tool, by centre and group; women with access to EMAeHealth who access the tool once; frequency of use of the tool, frequency of use of the different functions of the tool, etc).

Predictive, modifying and confounding variables: Patients: Age, parity, nationality, race, social class, educational level, marital status, work situation, distance to hospital, spontaneous pregnancy versus assisted reproductive technique, obstetric history and other clinical characteristics. Professionals: Sex, age, length of time in the position, type of contract, profile of adoption of innovations by professionals, measured by means of a questionnaire by Borracci *et al*, 2013.^36^ Health centres: reference IHOs, number of midwives and participation rate, rural or urban environment, and population served (figure 3).

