#### Study size

For the clinical effectiveness study, 18 centres will need to recruit 30 patients each, in each arm of the study (N=1080). This will make it possible to detect a difference of two points as significant in the mental component of the SF-36 test, with an alpha error of less than 5% and power greater than 80%. A 10-point SD is assumed for the mental SF-36 and an intracluster correlation of 0.01.

The calculation took into account the cluster design of the study and it was carried out using the National Institute of Health GRT sample size calculator* which assumes that the analysis will employ mixed-model regression methods.

* Research Methods Resources: National Institutes of Health. (Accessed on 2 January 2020). Available from: https://researchmethodsresources.nih.gov/grt-calculator

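### Centres are randomised within IHO strata, but the intention-to-treat model is described without an IHO term; if IHOs differ, the interval is conservative and some precision is forgone

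*Protocol article*

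**What the plan says.** The section 'Random assignment of centres' allocates centres "stratified by IHO and in a 1:1 ratio". It gives the reason for grouping in this way: "IHOs are groups of health centres within the same geographical area, with similar characteristics and population".

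'Statistical methods' sets out the main comparison: "quantitative comparisons will be made between intervention and control centres, with an intention-to-treat approach". The mixed models for it are those "which take into account the hierarchical structure of the data (patients grouped by midwives, midwives grouped by centre". The description stops at centre, one level below the randomisation stratum. The next analysis named, per protocol, is where covariates come in: the effect of using the tool "will be evaluated, adjusting for possible confounding factors". No such wording is attached to the intention-to-treat comparison.

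IHO is mentioned once more, under 'Outcomes', in the list of predictive, modifying and confounding variables: "Health centres: reference IHOs, number of midwives and participation rate". That list is not tied to a particular model.

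'Study size' states that "18 centres will need to recruit 30 patients each, in each arm of the study (N=1080". The aim is to "detect a difference of two points as significant in the mental component of the SF-36 test", with an SD of 10, an intracluster correlation of 0.01, alpha below 5% and power above 80%. It claims no gain from stratification.

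**The concern.** Stratified 1:1 allocation puts the two arms in the same IHOs in (near) equal numbers. Whatever the IHOs contribute to the outcome then largely cancels from the difference between arms. A model that knows only patients, midwives and centres cannot see this. It counts IHO differences as ordinary variation between centres and charges them to the standard error of the arm effect.

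The estimate stays unbiased, but its standard error is larger than the design warrants whenever IHOs differ. The test rejects less often than its nominal level, and part of the precision that stratification could have bought is not collected. With 36 centres and t-based power only just above 80% at complete data, that precision is worth having, though the sample size does not rely on it.

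**Working it through.** **Inputs from the article ('Study size').** 18 centres per arm, 30 women per centre, SD 10, intracluster correlation 0.01, difference 2 points. Sidedness is not stated; two-sided 5% is assumed, in line with the 95% confidence intervals. The total variance of 100 splits into 1 between centres and 99 within centres.

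**Assumed, because not stated.** f, the share of between-centre variance that lies between IHOs, from 0 to 1; S, the number of IHOs, from 5 to 13. Each IHO has equal numbers of centres per arm. The midwife level is ignored.

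**Step 1: reproduce the planned power.** The design effect is 1 + 29 × 0.01 = 1.29, so the effective number per arm is 540 / 1.29 = 418.6. A normal approximation gives 82.5%. With t on 36 − 2 = 34 degrees of freedom:

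- SE = √[2 × (1/18 + 99/540)] = √0.4778 = 0.691
- noncentrality = 2 / 0.691 = 2.89
- power = 80.3%

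The stated figure of above 80% is confirmed without any stratum term.

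**Step 2: the standard error that stratification delivers.** The IHO part drops out of the arm difference:

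- SE(f) = √[2 × ((1 − f)/18 + 99/540)]
- f = 0.5: √0.4222 = 0.650; f = 1: √0.3667 = 0.606

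Without an IHO term the model still reports about 0.691 (slightly less when there are few IHOs). With the term it reports SE(f), on 36 − 1 − S degrees of freedom: 30 for S = 5, 22 for S = 13.

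**Step 3: type I error without the term, f = 0.5.** The reported SE is too large by the factor 0.691 / 0.650 = 1.064. The effective critical value is 2.032 × 1.064 = 2.162, and the two-sided tail of t on 34 degrees of freedom beyond it is 3.8%.

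**Step 4: check by simulation.** 200,000 trials per setting, on centre means in balanced strata, for S = 5, 8, 9 and 13. Ranges run over S. The adjusted power and half-width come from the formula; the simulated adjusted power agrees to within about 0.2 points.

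| IHO share f | Type I error, no IHO term | Power, no IHO term | Power, IHO term (S = 5 to 13) | 95% CI half-width, IHO term (S = 5 to 13) |
|---|---|---|---|---|
| 0 | 5.0% | 80.3% (formula) | 80.0% to 79.0% | 1.412 to 1.433 |
| 0.25 | 4.4% | 80.9 to 81.2% | 82.3% to 81.3% | 1.370 to 1.391 |
| 0.5 | 3.8 to 4.0% | 81.8 to 82.1% | 84.6% to 83.7% | 1.327 to 1.348 |
| 1 | 2.8 to 3.1% | 83.4 to 84.1% | 89.2% to 88.4% | 1.237 to 1.256 |

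Type I error with the term was 4.9 to 5.1% throughout. The half-width without the term is about 2.032 × 0.691 = 1.405. The interval therefore narrows by about 5% at f = 0.5 and by at most about 12% at f = 1. At f = 0 it widens by 0.5 to 2.0%.

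**Step 5: a larger correlation.** If the intracluster correlation were 0.03 (an assumption) with f = 0.5 and S = 8, the same formulas narrow the interval by about 12%, and power is about 67% without the term and 76% with it.

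**The case against.** The strongest reply is that the quoted phrase describes clustering levels and is not a list of fixed effects. It does not mention baseline, time or even arm, so silence about IHO is not exclusion. A condensed article leaves the covariate list to the full protocol or the analysis plan, neither of which is shown, and IHO does appear among the possible covariates. Much of this stands: the article does not rule IHO out, and the analysis plan may already include it. But the article goes beyond saying 'mixed models'. It spells out which structure the model respects, stops short of the level used to stratify, and attaches adjustment only to the per-protocol analysis. An analyst who follows the text would fit a model that does not match the randomisation.

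A reader might also infer more than the article supports:

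- **That the interval is certainly too wide.** This depends on how far IHOs differ. The article says that centres within an IHO are alike; it does not say how much IHOs differ from each other.
- **That the trial is underpowered as a result.** The sample size used the unstratified design, and leaving IHO out does not take power below that plan.
- **That at a half share type I error falls to 3.1%, or that power rises from 80.3% to 84%.** The first figure puts a t critical value through a normal tail; the t tail gives 3.8%. The second compares a setting in which IHO explains nothing with one in which it explains half. Like for like, the gain is from about 82% to about 84%.
- **That a Wald z test would raise the error to about 5.8%.** The article names no reference distribution, so that concerns a test nobody has specified.

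**Conclusion.** The point holds as a modest, conditional one. The randomisation is stratified by IHO, and the intention-to-treat model as described does not reflect it. If IHOs differ, the consequence is a conservative interval and some lost precision; type I error is not inflated and the stated power is not undermined.

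At the planned correlation the loss is about 2 points of power if IHO carries half of the between-centre variance, and about 5 points if it carries all of it. If it carries none, there is no loss, and the term itself costs 0.3 to 1.3 points, which would put t-based power at 79.0 to 80.0%. These figures rest on an assumed share, an assumed 5 to 13 IHOs, balanced strata, equal centre sizes and complete data.

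**What to change.** Add one sentence to 'Statistical methods': the intention-to-treat arm comparisons include IHO, the randomisation stratum, as a fixed effect, alongside random intercepts for centre and midwife. If the analysis plan already says so, align the article's description with it. Settle this before outcome data are seen by arm, so that nobody later chooses between an adjusted and an unadjusted result.

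The change needs no new data, since each centre's IHO is known at randomisation. The cost is a few between-centre degrees of freedom: from 34 to between 30 and 22 for 5 to 13 IHOs.

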#### Study size

For the clinical effectiveness study, 18 centres will need to recruit 30 patients each, in each arm of the study (N=1080). This will make it possible to detect a difference of two points as significant in the mental component of the SF-36 test, with an alpha error of less than 5% and power greater than 80%. A 10-point SD is assumed for the mental SF-36 and an intracluster correlation of 0.01.

The calculation took into account the cluster design of the study and it was carried out using the National Institute of Health GRT sample size calculator* which assumes that the analysis will employ mixed-model regression methods.

* Research Methods Resources: National Institutes of Health. (Accessed on 2 January 2020). Available from: https://researchmethodsresources.nih.gov/grt-calculator

### Patient involvement

In the previous studies, multidisciplinary groups of midwives, nurses, paediatricians, epidemiologists, psychologists and pregnant and postpartum women were involved in the description and prioritisation of ME needs, as well as in the redesign of the ME and the design of an EMAeHealth tool to complement it.^3 6–8 8 15 21^ In this study, patients will be involved in testing the tool under construction, assessing its usability, acceptability and evaluating barriers and facilitators for its implementation in ‘real-world conditions’. In addition, women will participate as study subjects in the evaluation of the effectiveness of the digital tool.

## Ethics and dissemination

The study protocol has been reviewed and ethics approval obtained from the by the Clinical Research Ethics Committee of Euskadi, Spain in November 2020 (Ref: PI2020044). This approval covers all centres included in the study. Participation in this study will be voluntary; individual written (or online) consent will be sought from all participants. Each participant will receive a study information sheet that outlines the project and expectations in plain language
